***Consent***

**Study 1 and Study 2**

This study requires the general public aged over 65 to undertake an online surveys assessing their dementia awareness, motivation, alcohol consumption, smoking habits, general mental health and mood, quality of life, cognitive and physical activity levels, and an inventory of their social network. Participants will be required to provide identifiable information to be contacted to complete the same online surveys, 3 months later. Therefore, participants are consenting (1) participate in online surveys; (2) provide identifiable information at the first administration of the surveys and (3) complete the same surveys 3 months later; (4) contacted for a telephone interview to provide feedback on the campaign.

**Study 3**

This study requires the general public aged over 65 to undertake a new virtual reality cognitive screener (online) or a telephone-based cognitive assessment. Participants will be required to provide consent for researchers to use the identifiable information provided in study 1 to be contacted to participate in study 2. Therefore, participants are consenting to (1) using identifiable information provided in study 1 to be contacted for study 2; (2) participate in a virtual reality cognitive screener or; (3) participate in a traditional cognitive assessment via telephone (4) participate in an online feedback survey about the acceptability and feasibility of the Virtual Reality Cognitive Screener

Most research involving this population is premised upon the informed consent of the participants. If older participants are not competent enough to make a decision due to cognitive impairments, they will be excluded from the study. This is highlighted in the inclusion criteria.

Participant capacity to consent will be made explicit by them completing the survey and providing the research team with their online consent.

Information sheets and consent forms will provide an explicit outline of the study, participant involvement and expectations with a provision for “opt out” and Project Manager contact details for any queries. These documents will clearly state that the participants may opt out at any time.

### 6.6. DATA COLLECTION

**Study 1**

A widespread advertising strategy (**see Section 6.3**) will be used to recruit participants via the Brain Bootcamp website. Information about basic demographics (name, age, sex, phone number, address, marital status, education), dementia awareness, motivation, alcohol consumption, smoking habits, general mental health and mood, quality of life, cognitive and physical activity levels, and an inventory of their social network will be collected as described in **Section 7**. The surveys will take up to 25 minutes in total to complete. Participants will be provided with their individualised results in their Brain Bootcamp box alongside contact details of researchers if they wish to discuss their results.

**Study 2**

Participants who wish to participate in a telephone interview will share information on their views of the information they received from their profile, whether they have accessed the resources in their Brain Bootcamp box, any health behaviour change goals, how they did/did not incorporate recommendations into their daily life, and their perception of the overall impact of the campaign. Interviews will be audio recorded and will be sent of a to a professional transcribing service to be transcribed verbatim then the audio-recording destroyed. Typed transcripts will be edited to remove any identifying information. Each interview should take approximately 15 minutes.

**Study 3**

Participants will be recruited from the general public who are over 18. Study 1 participants will be contacted to give them an opportunity to participate in Study 3, based on their brain health risk scores. Information about their memory performance will be collected as outlined in **Section 7.** Both the Virtual Reality Cognitive Screener and telephone based cognitive assessment will take approximately 30 minutes to complete. A random selection of half of each of the younger and older adults participants will receive the traditional telephone cognitive assessment (Group A), whilst the other half will complete the Virtual Reality Cognitive Screener (Group B). Then, the groups will swap and Group A will complete the Virtual Reality Cognitive Screener , whilst Group B completes the telephone cognitive assessment. Both assessments will then be complete within a week of each other. After completion of the virtual reality cognitive screener, participants will be invited to provide feedback via a voluntary online survey about the feasibility and acceptability of their virtual reality experience.

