**Study 2**

Based on a power analysis for biserial correlation using G*Power 3 with a conservative medium effect of ρ = .30 [47]report very high effect sizes with a similar design), and 80% power, an N of 64 is required to detect an association at p = .05 for each group. The final proposed sample size (N=100 per group) was larger than required for the present study to account for potential drop-outs between assessments.

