**Study 3**

Descriptive data will be compared between the groups using a two-sample t test and the Fisher exact test for continuous and categorical variables, respectively. Summary statistics will be calculated individually for the Virtual Reality Cognitive Screener, traditional cognitive assessment and questionnaire-dependent feedback scores. Younger and older adults (and older adults with cognitive impairment) cognitive performance on all measures will be compared using the two-sample t tests.

Performance scores will be analysed at each task level, given a total score, and compared between the older cognitive-intact and younger groups using the methods described above, as appropriate. Correlation between performance scores and other variables will assessed using Pearson correlation. A logistic regression will performed based on the total performance scores, followed by ROC analysis to assess its predictive capability to discriminate between cognitively intact and cognitively impaired individuals. Analyses will be performed using SPSS V22.0.

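### Study 3 randomises test order, but the planned screener–TICS-M correlation leaves order out; a partial correlation adjusted for order would protect it at the cost of one degree of freedom

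*Protocol*

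**What the plan says.** Section 6.6 of the protocol (Study 3) allocates test order at random within each age group. "A random selection of half of each of the younger and older adults participants" forms Group A, which takes the TICS-M by telephone first; the other half, Group B, takes the virtual reality screener first. "Then, the groups will swap and Group A will complete the Virtual Reality Cognitive Screener" while Group B takes the telephone test. On timing: "Both assessments will then be complete within a week of each other".

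Section 8.2 (Study 3) sets out the analysis. "Correlation between performance scores and other variables will assessed using Pearson correlation", and the Summary's analysis plan makes clear that these other variables include scores on the traditional cognitive tests. Two-sample t tests, Fisher exact tests, logistic regression and an ROC analysis are also named. The comparisons described are between younger, older and cognitively impaired older adults. Neither Group A/B nor any order, sequence or period term appears.

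The sample size is in section 8.1, in a block headed Study 2 that describes Study 3. "Based on a power analysis for biserial correlation using G*Power 3", it assumes a "conservative medium effect of ρ = .30" and concludes: "80% power, an N of 64 is required to detect an association at p = .05 for each group". It adds that "The final proposed sample size (N=100 per group) was larger than required for the present study", the excess being an allowance for drop-out between assessments.

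**The concern.** Counterbalancing is commonly taken to deal with order effects. It does so for means: with order split evenly within each age group, a second-test gain is shared equally by younger and older adults. A correlation pooled over the two orders is different. Group A would tend to be higher on the screener and Group B higher on the TICS-M for no reason other than order. That opposing pattern enters the covariance and pulls the correlation down. If one test gains and the other loses when taken second, the pattern reverses and the correlation is inflated, which would overstate convergent validity for an instrument that the protocol itself describes as not yet validated.

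Some order effect is plausible from the protocol's own description in section 7. Both instruments include immediate and delayed recall. Feedback also differs: participants are given their TICS-M result at the end of that session, but after the screener they learn only how many orders were correct. Group A can therefore start its second test knowing its TICS-M score.

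At stake are the size of the main convergent-validity estimate and, in some scenarios, the power to detect it.

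**Working it through.** **Inputs from the protocol.** ρ = 0.30, 80% power, significance level 0.05 with sidedness not stated, 64 needed and 100 planned per group (section 8.1); 1:1 random order within age group, both tests taken by everyone (section 6.6).

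**Input assumed.** d, the shift in SD units of whichever test is taken second. The protocol gives no value, so a range is shown.

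**1. The stated 64.** Under the point-biserial model, the noncentrality is √n·ρ/√(1 − ρ²), with n − 2 degrees of freedom. At n = 64 this is 8 × 0.30/√0.91 = 2.516. A one-sided test at 0.05 then has 80.05% power, so 64 is reproduced. Other versions do not give 64: two-sided point-biserial needs 82, Fisher z one-sided 68, and Fisher z two-sided 85.

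**2. Effect of order on a pooled correlation.** Take within-order SDs of 1 and correlation ρ. With equal halves and a gain of d on the second test:

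- Group A lies d/2 above the overall mean on the screener and d/2 below it on the TICS-M; Group B is the reverse.
- Between-order covariance: −(d/2)(d/2) = −d²/4.
- Extra variance on each test: d²/4.
- Same direction on both tests: r = (ρ − d²/4)/(1 + d²/4).
- Opposite directions: r = (ρ + d²/4)/(1 + d²/4).
- One test only: r = ρ/√(1 + d²/4).

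For d = 0.3, d²/4 = 0.0225. Same direction gives 0.2775/1.0225 = 0.271; opposite directions give 0.3225/1.0225 = 0.315. For d = 0.5, d²/4 = 0.0625. Same direction gives 0.2375/1.0625 = 0.224; opposite directions give 0.3625/1.0625 = 0.341; one test only gives 0.30/√1.0625 = 0.291.

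**3. Power without adjustment, same-direction shift** (point-biserial model):

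| d (assumed) | r | n = 64, one-sided | n = 100, one-sided | n = 100, two-sided |
|---|---|---|---|---|
| 0 | 0.300 | 80.1% | 93.0% | 87.6% |
| 0.1 | 0.297 | 79.2% | 92.5% | 86.8% |
| 0.2 | 0.287 | 76.6% | 90.9% | 84.3% |
| 0.3 | 0.271 | 72.1% | 87.6% | 79.7% |
| 0.4 | 0.250 | 65.5% | 82.1% | 72.5% |
| 0.5 | 0.224 | 56.7% | 73.6% | 62.2% |

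At n = 100, power falls below 80% once d exceeds about 0.43 (one-sided) or 0.30 (two-sided). At n = 64 there is almost no reserve: the limit is about d = 0.02. With a 0.5 SD shift on one test only, one-sided power is 77.7% at 64 and 91.6% at 100.

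**4. With order adjusted for.** The partial correlation returns to about 0.30 whatever d is, and one degree of freedom is lost. One-sided power is 79.5% at 64 (65 restores 80%) and 92.8% at 100; two-sided power at 100 is 87.2%.

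**5. Simulation check** (20,000 runs per scenario, n = 100, d = 0.5). The mean unadjusted r is 0.222 with 72.8% one-sided power; the mean adjusted r is 0.299 with 91.9%. This agrees with the formulas to within about one percentage point.

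**The case against.** The strongest reply is that the harm is assumed. Nothing in the protocol gives or expects an order effect. The two instruments are also quite different: the TICS-M covers orientation, counting, naming and repetition as well as word recall, while the screener is a waiter game scored on food orders and placement. No shared items are described, so an equal gain of 0.3 to 0.5 SD on both is far from certain. This stands, and it is why every size above is conditional on d.

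A second reply is that adjustment for a counterbalancing factor is usual material for a statistical analysis plan, which may exist and is not shown. That has some force. However, section 8.2 is headed as a detailed plan and itself names an unadjusted Pearson correlation, so a later plan that adjusts for order would have to depart from it.

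Three stronger readings are tempting and are not supported:

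- **Study 3 will miss its stated 80% power.** At 100 per group, on the basis that reproduces 64, power stays above 80% for small and moderate effects. A fall to just under 80% at d = 0.3 needs a two-sided test, which is not the basis that reproduces 64.
- **The younger–older t tests are compromised.** Order is balanced within each age group, so those means are compared fairly. The cost is a variance increase of d²/4, about 2% at d = 0.3.
- **Order belongs in the logistic model and ROC as well.** The ROC would then describe score plus test order rather than the screener. Order could move people across a TICS-M cut-off, but that is not quantified here, and a covariate would not correct the reference labels.

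**Conclusion.** The point holds in a limited form. The protocol randomises order and then names a correlation that does not use it, and counterbalancing alone does not protect that correlation. From ρ = 0.30, an assumed same-direction shift of 0.2 to 0.5 SD on both tests lowers r to between 0.287 and 0.224. Opposite shifts of 0.3 and 0.5 SD raise it to 0.315 and 0.341. A shift on one test alone leaves it at 0.291 or higher for d up to 0.5.

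Power is a secondary matter. It is exposed if drop-out takes a group towards 64, and well protected at 100 unless the shift on both tests is sizeable. These figures rest on equal shifts on the two instruments, an even split by order, and the one-sided point-biserial reading of the sample size unless marked two-sided. This is a free improvement to the analysis, not a flaw in the design.

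**What to change.** In section 8.2 (Study 3), state that the association between the screener and the TICS-M will be estimated within each age group as a partial correlation adjusted for the randomised order (Group A or B). Report mean scores on each instrument by order, so that readers can see whether an order effect occurred. Keep the ROC on the screener score alone, with no order term in the classifier, and leave the younger–older t tests as they are.

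The cost is one degree of freedom, equivalent to 65 instead of 64 per group for 80% power on the protocol's own basis and already covered by the planned 100. No new data are needed, provided the Group A/B allocation is kept in the analysis file.

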### 6.7. END OF STUDY WITHDRAWAL PROCEDURE

Participants will receive a summary written specifically for their understanding of the aggregate results if they wish.

### 6.8. PATIENT WITHDRAWAL

Participants will be able to withdraw at any point of the study if they no longer want to be involved. Participants can withdraw by informing the researchers.

# 7. OUTCOME MEASURES

Participants will have the following measures assessed at two time points (baseline and three months later). A summary of measures used in the current study are provided in **Table 2**, with further detail below.

**Table 2. Assessment measures for participants**

| Study 1 | | |
| --- | --- | --- |
| Outcome | Data collection instrument | |
| Primary Outcomes | | |
| Dementia Awareness | Dementia Awareness Questionnaire [22, 23] | |
| Brain health risk profile | LIBRA index [19] | |
| Motivation | Motivation to Change Lifestyle and Health Behaviour for Dementia Risk Reduction (MCLHB-DRR)[24] | |
| Quality of life | EuroQol Group EQ-5D-5L [25] | |
| Social networks | Lubben Social Network Scale (LSNS-6) [26] | |
| Overall experience | Impact Evaluation survey [27] | |
|  |  |  |
| Study 2 | | |
| Outcomes | | |
| Behaviour change/ impact of campaign | Semi-structured interviews | |
| Study 3 | | |
| Outcomes | | |
| Memory performance | Virtual reality assessment (developed in house by our researchers)  Telephone Interview for Cognitive Status-Modified (TICS-M) | |
| Acceptability | Research-team generated feedback survey | |

**Study 1**

**Dementia awareness:** Dementia awareness and literacy will be measured using the Dementia Awareness Questionnaire [23]. This questionnaire includes ten items from the UK’s BSA survey [22], assessing self-reported knowledge of dementia, personal experience with people with dementia, dementia risk awareness and knowledge of four modifiable dementia risk and protective factors (i.e., hypertension, smoking, physical activity, depression and diabetes). We will further include nine additional modifiable risk and protective factors (i.e., obesity, coronary heart disease, chronic kidney disease, hypocholesteraemia, mental activity, low to moderate alcohol intake, healthy diet, midlife hearing loss and social connections), in order to assess all the known modifiable risk and protective factors in the literature [28, 29]. In addition, three sham factors will be included (use of painkillers, personal hygiene and having children) to check for monotone answering tendency. Additional items will be developed to evaluate the needs, wishes and barriers of participants concerning brain health, such as the need for further information, preferred information source, subjective barriers to engage in a brain-healthy lifestyle, and motivation to use an internet application to increase risk factor awareness. Most items will be set up as statements. Participants will be asked to what extent they agree or disagree on a 5-point Likert scale ranging from ‘strongly disagree’ to ‘strongly agree’. Improvements in dementia literacy are defined as the presence of one to three standard deviations improvement on the questionnaire compared to baseline.

**Demographics** including age, gender, income, marital status, address, , education level (as identified by completed years of schooling and tertiary studies)

**Depression:** Participants will self-report depressive symptoms using the 9-item brief depression severity measure, Patient Health Questionnaire (PHQ-9). Responses range from 0 (“not at all”) to 3 (“nearly every day”) [30]. It has been used in several contexts including medical settings and amongst the general population [31] and has a sensitivity and specificity of 88% for major depression [30]. A score 10 or above indicates symptoms of minor depression, dysthymia or major depression (mild)

**Physical activity:** Levels of physical activity will be measured based on the short LIBRA administration used in the *MijnBreincoach app* developed for online administration*.* It consists of one question with three possible responses “Yes” (0), “A little” (0) and “No” [23].

**Social networks:** will be measured using the 6-item version of the Lubben Social Network Scale (LSNS-6). Internal reliability (0.83) is good and the two sub-scales (family and friendships) both demonstrate high levels of internal consistency. Scores range from 0-30 with higher scores indicating more social engagement and scores < 12 identifying individuals at risk of social isolation[26].

**Quality of life:** will be measured using the EQ-5D-5L scale. It consists of a self-administered health index and a 100-point visual analogue scale (VAS), for participants to rate their current health state from 0 as their ‘worst imaginable health state’ to 100, their ‘best imaginable health state’ [25]. The instrument covers mobility, self-care, pain/discomfort, usual activities and anxiety/depression[32]. Utility scores are quantified along a continuum that ranged from -0.59 (worst health) to 1.00 (perfect health). It has demonstrated convergent validity [33] and good reliability for individuals with diverse health conditions [34, 35].

**Cognitive activity:** Will be measured using Adapted Cognitive Reserve questionnaire (CRIq)[36]. This 20 item instrument measures cognitive activity across three sections; education (e.g. years of education, training courses), working activity (e.g. adulthood professions) and leisure time (e.g. reading newspaper, playing music, social and physical activities)[36]. Performance below the cut-off in at least 2 sections indicates a lower risk of cognitive impairment [37] This instrument has established construct validity in unhealthy populations.

**Diet:** adherence will be measured using the Mediterranean Diet Adherence Screener (MEDAS)[38]. This is a validated[39] a 14-item scale and a score of 0 or 1 is assigned to each item. A maximum score of 14 indicates the greatest adherence to the diet.

**Motivation:** Motivational attitudes and beliefs to modify lifestyle specific to dementia risk reduction will be measured using Motivation to Change Lifestyle and Health Behaviour for Dementia Risk Reduction (MCLHB-DRR)[24]. This is a 27-item tool, commonly used in the evaluation of dementia prevention programs. It has been validated amongst individuals aged 50 and over with moderate to high internal reliability and test-retest reliability.

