**Other factors**

- Heart disease (heart or blood vessel condition; yes, no, I don’t know);
- Low to moderate alcohol consumption (standard units consumed per day);
- Smoking habits (i.e. current smoker; yes or no);
- Chronic kidney disease (yes, no, I don’t know)
- Cholesterol (High cholesterol; yes, no, I don’t know)

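### Dementia-literacy improvement is defined by a closed band of one to three SDs, with the SD, level and scored items unstated and no link to the planned analysis

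*Protocol*

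**What the plan says.** Study 1 objective (i) (Section 3.1) is to increase dementia awareness and knowledge of modifiable factors. Hypothesis 2 repeats it, and the Summary's analysis plan and Table 2 both list dementia awareness as a primary outcome.

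Section 7, Dementia awareness, names the instrument: "Dementia awareness and literacy will be measured using the Dementia Awareness Questionnaire". It gives one definition of success: "Improvements in dementia literacy are defined as the presence of one to three standard deviations improvement on the questionnaire compared to baseline".

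The same paragraph describes what the questionnaire holds:

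- The core items cover several things: "assessing self-reported knowledge of dementia, personal experience with people with dementia, dementia risk awareness", plus knowledge of named risk and protective factors. The text announces four such factors but lists five. Nine more are added.
- There is a response-style check: "three sham factors will be included (use of painkillers, personal hygiene and having children) to check for monotone answering tendency".
- There are items that do not measure knowledge: "Additional items will be developed to evaluate the needs, wishes and barriers of participants concerning brain health".

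The analysis text does not use the definition. The Summary names non-parametric correlations and paired t-tests for change in awareness and in the brain health risk profile. Section 8.2 keeps the paired t-test for the risk profile only. It calls awareness a secondary outcome, to be correlated with change in the primary outcome.

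**The concern.** An improvement rule should have a floor and no ceiling. This one has both, so its wording classes the largest gains as something other than improvement. It also leaves open three matters that decide the answer: baseline SD or SD of change, participant or group mean, and which items make up the score.

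Because the rule is separate from the analyses, the same data could give a clearly significant mean gain in a paired test and no improvement under the definition. The protocol does not say which would decide objective (i). Nothing limits the rule to knowledge items either, so a shift in answers on personal experience or barriers is not ruled out as a contribution to literacy.

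What is at stake is the conclusion drawn on a primary objective. The rule feeds no planned test or sample size, so error rates and power are unaffected.

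**Working it through.** The protocol attaches no responder rate, power or sample size to the rule, so there is no figure to reproduce. The calculations show what the wording does under each reading.

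**Inputs from the protocol.** Floor 1 SD and cap 3 SD (Section 7); planned recruitment 500 (Section 4.2); 403 needed, 25% dropout, 90% power, α = 0.05 (Section 8.1; two-sided assumed here).

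**Assumptions, not in the protocol.** Equal SD at both visits, normally distributed gains, pre-post correlation r from 0.5 to 0.8, and true mean gain m from 0 to 2 baseline SD.

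**Group-mean reading.** The smallest mean change that a paired test detects with 90% power is (1.960 + 1.282)/√n, in units of the SD of change.

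- 500 × 0.75 = 375 completers: 3.242/√375 = 0.17.
- 403 × 0.75 = 302 completers: 3.242/√302 = 0.19.

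The SD of change is √(2(1 − r)) baseline SDs, that is 1.000 at r = 0.5 and 0.632 at r = 0.8. In baseline SDs the detectable change is therefore 0.11–0.17 (375) or 0.12–0.19 (302). On either choice of SD, any mean gain from there up to 1 SD would be reliably detected yet classed as no improvement.

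**Participant reading, baseline SD.** The gain D is Normal with mean m and SD √(2(1 − r)). Then P(D ≥ 1) = 1 − Φ((1 − m)/SD) and P(D > 3) = 1 − Φ((3 − m)/SD).

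| True mean gain m | In the 1–3 band, r = 0.5 / 0.8 | Above 3 SD, r = 0.5 / 0.8 | Gain between 0 and 1, r = 0.5 / 0.8 |
|---|---|---|---|
| 0 | 15.7% / 5.7% | 0.1% / <0.1% | 34% / 44% |
| 0.5 | 30.2% / 21.5% | 0.6% / <0.1% | 38% / 57% |
| 1.0 | 47.7% / 49.9% | 2.3% / 0.1% | 34% / 44% |
| 2.0 | 68.3% / 88.6% | 15.9% / 5.7% | 14% / 6% |

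Adding the first two columns gives the share that reaches the floor. At m = 0.5 it is 1 − Φ(0.5) = 31% for r = 0.5 and 1 − Φ(0.791) = 21.5%, about 22%, for r = 0.8. At m = 0 it is 1 − Φ(1) = 16% and 1 − Φ(1.581) = 6%.

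**Participant reading, SD of change.** With r = 0.8, a mean gain of 0.5 baseline SD equals 0.5/0.632 = 0.79 SD of change. The share reaching 1 SD is then 1 − Φ(1 − 0.79) = 42%, about twice the 22% found with the baseline SD. At r = 0.5 the two SDs coincide. The unstated choice of SD therefore changes the reported rate materially.

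**The case against.** The strongest reply is that the sentence appears once and governs nothing: no test, sample size or decision depends on it, and the Summary already plans a paired comparison for awareness. That stands in part. The damage is confined to interpretation, and the main remedy is already named. However, Section 8.2 drops that comparison, and the band remains the only stated definition of improvement for this outcome.

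A second reply is that item scoring is often left to a SAP, and none was available for this review. That is fair for the scoring key. It does not cover the band, which the protocol itself fixes. A minimum of 1 SD is also not wrong in itself as a responder threshold.

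A reader might infer more than the protocol supports:

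- **That the cap discards many successes.** It does so only for very large gains; 6–16% needs a mean gain of 2 SD.
- **That the floor conflicts with the effect used to size the study.** The inputs in Section 8.1 (0.3 with SD 0.5) are for dementia risk scores. They cannot be carried over to literacy.
- **That a total mixing knowledge with other items will be scored, so that general agreement counts as literacy.** No total is stated, and the sham items are there to detect indiscriminate agreement. The supported point is that the score is undefined and not limited to knowledge.
- **That the protocol contradicts itself on cholesterol.** The awareness list has "obesity, coronary heart disease, chronic kidney disease, hypocholesteraemia, mental activity", while the Other factors list has "Cholesterol (High cholesterol; yes, no". The first is a knowledge item in a list of both risk and protective factors; the second asks about the participant's own health. The term may be a slip and merits a check, but the two lists do not conflict.

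**Conclusion.** The point holds as a fault in the definition and in its link to the analysis. As written, the band excludes gains above 3 SD and, on the group reading, statistically clear mean gains anywhere from about 0.2 SD up to 1 SD. The SD, the level and the scored items are unstated, and the Summary and Section 8.2 differ on how awareness is analysed.

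The 1 SD floor matters most. At a true mean gain of 0.5 baseline SD about 22–31% of participants reach it, and with no true change 6–16% do. Study 1 has no control group, so that chance rate cannot be separated from benefit in an observed responder rate. The cap is mainly a wording defect: under 1% at a mean gain of 0.5 SD and 0.1–2.3% at 1 SD. The percentages rest on normal gains, equal SDs and r between 0.5 and 0.8. The objections to the wording do not depend on them.

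**What to change.** 1. In Section 8.2, restore the paired analysis of awareness that the Summary names, and judge objective (i) by the mean pre-post change with its 95% CI. Align the primary or secondary label with the Summary and Table 2.
2. In Section 7, base the score on the risk- and protective-factor knowledge items. Leave out the personal-experience and needs, wishes and barriers items. Use the sham items as the response-style check, for example by reporting their change alongside the main result.
3. Replace the band. If a responder rate is kept, define it per participant as a gain of at least 1 baseline SD with no upper limit, and label it descriptive.
4. Reconcile the count of four with the five factors listed, and check the wording of the hypocholesteraemia item before it is keyed.

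The cost is a few sentences in Sections 7 and 8.2 and one item check. No added participants, visits or instruments are needed, since the knowledge and sham items are already part of the planned questionnaire.
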